### Recruitment and promotion of participant retention

Because encephalopathy with ESES is relatively rare, we initiated a collaboration with European centres with a high level of expertise in epilepsy. The trial was announced at several international congresses, in newsletters of national and international paediatric neurology and epilepsy associations, and in patient magazines. Online as well as local training meetings for study personnel were organised. The study team is available for any questions or concerns from patients and their parents, and an independent physician is available for questions or complaints. If patients discontinue participation in the study or a protocol deviation occurs, the baseline and outcome measures that have been collected before discontinuation will still be analysed, e.g. if discontinuation occurred after 6 months of follow-up, the collected data will be included in primary outcome assessment. If they switch to the other treatment arm, but agree to continued follow-up according to the study protocol, their outcomes will still be analysed in the intention-to-treat analysis.

### Safety and tolerability

In accordance with legal requirements, the investigator will inform study participants and the reviewing accredited Ethics Committees (EC) if any data or findings emerge during the conduct of the study that suggest that risks involved in participation may outweigh potential benefits. Considering that both study medications have been widely prescribed for many years and their side effect profiles are well-known, the occurrence of suspected unexpected serious adverse reactions (SUSARs) is unlikely. The sponsor has a liability insurance which is in accordance with the European Clinical Trial directive 2001/20/EC. The sponsor also has an existing participant insurance which is in accordance with the legal requirements in the Netherlands. In all participating centres, a participant insurance has been contracted if there was no existing patient insurance that applies for the current study, unless an exemption of insurance requirements was possible considering the pragmatic design of the study, closely resembling current clinical practice.

Adverse events will be specifically asked for during the study visits, and parents of study participants will be instructed to contact their treating physician if any serious event will occur. In addition, general practitioners of participants will be informed of study participation and asked to contact the study team if any adverse events will be noted.

Adverse events will be reported according to Good Clinical Practice (GCP) guidelines. Adverse events are defined as any undesirable medical experience occurring to a subject during the study, whether or not considered related to the investigational drug. A serious adverse event (SAE) is any untoward medical occurrence or effect that at any dose results in death, is life-threatening, requires hospitalisation or extension thereof, results in persistent or significant disability or incapacity or otherwise jeopardises the subject, or requires intervention. SUSARs are SAEs that probably relate to the investigational drug and that are unexpected with regard to the drug used. If there is any uncertainty regarding relation between the study medication and a severe adverse event, this will be discussed within the steering committee of the trial. All adverse events are recorded and reported by the sponsor. SAEs will be reported to the ethics committee that approved the study within 15 days and followed up until they have abated or until a stable situation has been reached. SUSARs will be reported to the ethics committee and competent authority of the country where the SUSAR occurred within 15 days, and for fatal or life-threatening cases, a preliminary report will be sent within 7 days. The SUSAR will be reported to the EMA EudraVigilance database. A developmental safety update report (DSUR) will be provided annually to the ethics committees and competent authorities. An overview of adverse events per study treatment will be included in the final trial publication.

We will perform an interim analysis by the time primary outcome can be analysed in half of the required patients to evaluate whether there are unexpectedly large differences in effectiveness and unexpected side effects in both treatment groups. This analysis will form the basis to determine whether continuation of the trial is ethically justified.

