Treatment will be continued for at least 6 months, unless informed consent is withdrawn, the patient develops intolerable adverse effects, or further cognitive regression occurs, requiring an alternative intervention in the opinion of the treating physician. If cognitive regression is observed to continue after 3 months of treatment, according to the impression of the parents or physician, switching to the other treatment arm is allowed. In patients requiring switching to an alternative treatment, an EEG will be obtained before switching.

Drug adherence to oral treatment (oral clobazam or oral prednisolone) will be optimised and monitored by instructing patients to bring their empty packages of study medication to the hospital at every scheduled visit, together with completed drug intake diaries. In addition, for patients treated with clobazam, plasma levels will be measured in blood samples collected between 1 and 3 months after enrolment and between 3 and 6 months after enrolment. For intravenous methylprednisolone, adherence will be confirmed by recording drug administration at times of hospital admission for the monthly pulses.

Concomitant medication will be allowed as long as the patient fulfils the criteria for inclusion. However, changes in concomitant medications are discouraged during the first 6 months. After assessment of the primary endpoint at 6 months, subsequent treatment strategies will be left to the clinical judgement of the treating physician.

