### Outcomes

The co-primary outcome measures at 6 months will be cognitive functioning, assessed with a full neuropsychological assessment (NPA):
Intelligence quotient (IQ), or developmental quotient (DQ), compared to baseline IQ/DQ. Improvement is defined as an increase by 10 IQ/DQ points.Cognitive sum score (as defined below). Improvement is defined as statistically significant when improved by at least 75% of the standard deviation (SD).

Secondary outcome measures at 6 and 18 months will include the following:
Changes in individual absolute test results, and IQ/DQ scores, compared to baseline.Changes in spike wave index (SWI) during non-REM sleep, compared with baseline SWI.Changes in seizure frequency assessed for all reported seizure types combined, with improvement being defined as at least 50% decrease as compared with baseline.Changes in subjective global daily functioning assessed with a visual analogue score (VAS) of − 5 to + 5 as compared with baseline.Safety and tolerability, as assessed by the occurrence of adverse events.Change in inflammatory markers post-treatment as compared to levels prior to treatment.Identification of autoantibodies as potential biomarkers of disease severity (TIQ, presence of developmental regression, arrest, or delay and SWI at baseline) and treatment efficacy.

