### Statistical analysis

The primary analyses will be performed according to the intention-to-treat principle. We will also perform (secondary) analyses in patients who have completed their assigned treatment for the period of 6 months.

Continuous outcomes will be presented with means and 95% confidence intervals. These outcomes will primarily be compared between the two treatment groups using a *t* test or Mann-Whitney *U* test depending on the distribution of the data (normal vs not normal). Categorical outcomes will be presented as proportions with 95% confidence intervals. These outcomes will primarily be compared between the two treatment groups using Fisher’s exact test. Rates of (serious) adverse events will be compared in terms of risk ratios with corresponding 95% confidence intervals. We will also identify the proportion of patients that continue on the initially allocated treatment throughout the entire study period, and analyse possible predictors for discontinuation.

Although the stratified randomisation procedure intends to create two groups with equal patient characteristics, it is known that in randomised trials of < 1000 patients, there still is a risk of bias by chance [25]. Adjusted analyses are often performed to reduce the influence of the possible differences between the two treatment arms [26]. Therefore, possible predictors of treatment outcome (i.e. known prognostic factors) will be included in a multivariate logistic/linear regression model. These prognostic factors are as follows: age at ESES recording, time interval between ESES recording and inclusion, IQ levels and cognitive sum scores at enrolment, number of drugs administered before enrolment, and aetiology (unknown, structural, metabolic, genetic, immune, infectious). We will also include cytokine and autoantibody profiles as possible predictors.

The prospective design and structured follow-up schedule should minimise the amount of missing data. However, to account for possible influence of missing data, we will perform a sensitivity analysis using multiple imputation methods [27].

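### The serious adverse event definition ends with an unqualified need for intervention, so treated minor events may be counted as serious, inconsistently across sites and unequally between arms

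*Protocol article*

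**What the plan says.** The definitions are in the protocol article under Safety and tolerability. The starting pool is wide: "Adverse events are defined as any undesirable medical experience occurring to a subject during the study", whether or not related to the drug. An event becomes serious if it is fatal, life-threatening, or leads to or prolongs a hospital stay, or if it "results in persistent or significant disability or incapacity or otherwise jeopardises the subject, or requires intervention". The last criterion is joined by its own conjunction and carries no limit on severity, on type of intervention or on the outcome to be averted. No other part of the article narrows it.

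Four uses depend on this definition:

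- Statistical analysis: "Rates of (serious) adverse events will be compared in terms of risk ratios with corresponding 95% confidence intervals".
- Safety and tolerability: every SAE goes to the approving ethics committee within 15 days.
- Safety and tolerability: "SUSARs are SAEs that probably relate to the investigational drug and that are unexpected with regard to the drug used", so the expedited class is drawn from the SAEs.
- Monitoring: monitors check the presence and correctness of all SAEs. There is no data safety and monitoring board.

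Under Outcomes, the secondary safety endpoint is "Safety and tolerability, as assessed by the occurrence of adverse events".

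**The concern.** Taken at its word, the last criterion makes the label depend on whether someone acted, not on how grave the event was. A mild infection given a prescription would qualify. So would many of the effects that the Background expects (weight gain and raised glucose with corticosteroids, sedation and agitation with clobazam), once a clinician responds to them.

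Two consequences follow if sites use it that way. First, the SAE category loses meaning: the analysis would mix grave events with treated minor ones, and the 15-day reports would carry both. Second, counts may not be comparable. Preparations cover 22 centres in 12 countries, and some may read the clause literally and others narrowly.

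Randomisation is stratified by centre, so a difference in reading between centres is shared by both arms. That does not make the effect equal between arms, because the chance that an event is found and acted on can differ by treatment. Under Treatment, patients and treating physicians know the allocation. Under Data collection during follow-up, blood pressure, glucose, urine protein and weekly weight checks are specified as additional for the corticosteroid group. The article expects corticosteroids to bring more frequent or more severe side effects, so this comparison is one that readers will look at.

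**Working it through.** The article states no SAE rate and no SAE risk ratio, so there is no figure of the plan's own to reproduce here. The sample size (116 evaluable, 130 enrolled) rests on the proportions of treatment success and takes no safety input. What follows illustrates how the wording could act. **All event risks are assumptions.** Only the 65 children per arm come from the article.

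**Model.** Let *s* be the risk of a truly serious event and *m* the risk of at least one treated minor event, taken as independent. Under the literal wording the SAE risk in an arm is

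*p* = 1 − (1 − *s*)(1 − *m*),

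and the risk ratio is *p* (corticosteroids) / *p* (clobazam). The 95% interval is exp{ln RR ± 1.96 × √[(1 − p₁)/(65 p₁) + (1 − p₂)/(65 p₂)]}.

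**Case A: equal minor-event risk.** *s* = 0.08 and 0.04, so the ratio for truly serious events is 2.0.

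| *m* in each arm | Corticosteroids | Clobazam | Ratio |
|---|---|---|---|
| 0.15 | 1 − 0.92 × 0.85 = 0.218 | 1 − 0.96 × 0.85 = 0.184 | 1.18 |
| 0.30 | 1 − 0.92 × 0.70 = 0.356 | 1 − 0.96 × 0.70 = 0.328 | 1.09 |
| 0.50 | 1 − 0.92 × 0.50 = 0.540 | 1 − 0.96 × 0.50 = 0.520 | 1.04 |

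With equal minor-event risks the ratio is pulled towards 1.

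**Case B: unequal minor-event risk** (corticosteroids first).

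| *s* | True ratio | *m* | SAE risks | Ratio (95% CI) |
|---|---|---|---|---|
| 0.10, 0.05 | 2.00 | 0.40, 0.20 | 0.46, 0.24 | 1.92 (1.15 to 3.18) |
| 0.10, 0.05 | 2.00 | 0.20, 0.40 | 0.28, 0.43 | 0.65 (0.40 to 1.05) |
| 0.05, 0.05 | 1.00 | 0.40, 0.20 | 0.43, 0.24 | 1.79 (1.07 to 3.00) |
| 0.05, 0.05 | 1.00 | 0.20, 0.40 | 0.24, 0.43 | 0.56 (0.33 to 0.93) |

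Worked interval for the third row: ln(0.43/0.24) = 0.583; the standard error is √[0.57/27.95 + 0.76/15.6] = √(0.0204 + 0.0487) = 0.263; exp(0.583 ± 0.515) = 1.07 to 3.00.

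The ratio may therefore stay almost where it was (2.00 to 1.92), reverse (2.00 to 0.65), or show a difference where there is none (1.00 to 1.79 or 0.56). In the last two rows the interval excludes 1 although the risks of truly serious events are the same.

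**The case against.** The best defence is that sites will not read the clause literally. It follows directly on jeopardy to the subject, at the end of a list of grave outcomes. The same section states that "Adverse events will be reported according to Good Clinical Practice (GCP) guidelines", all SAEs are checked for correctness, and training meetings were held. The article also condenses a full protocol that may hold the limiting words. This stands in part: it makes a narrow reading plausible, so misclassification is a risk and not a certainty. It does not repair the sentence. Correctness has to be checked against a definition, and the one printed is too broad. This is a stated rule, not an omitted detail.

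It is also fair that the overall adverse event comparison does not use the seriousness label, and that the SAE ratio will be imprecise in any case. With correctly classified risks of 10% and 5% and 65 per arm, a ratio of 2.00 has a 95% interval of 0.55 to 7.24. Both points limit the damage. Neither helps the reader of a contaminated ratio, whose interval can look tighter because it counts more events.

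A reader might infer three stronger things that the article does not support.

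- *The SAE ratio will certainly fail to measure serious harm, or will certainly be diluted.* Without event rates or evidence of how sites apply the clause, neither follows.
- *The hospitalisation criterion is biased against the corticosteroid arm.* For intravenous methylprednisolone, "adherence will be confirmed by recording drug administration at times of hospital admission for the monthly pulses", so a longer stay might seem an artefact of that arm. But a planned admission is not an untoward occurrence, a prolonged stay is an explicit seriousness criterion whose narrowing is debatable, and part of the arm may receive oral prednisolone.
- *SAEs already filed should be downgraded one by one.* In an open-label trial that carries its own risk of bias.

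**Conclusion.** The point holds as a defect of wording that can affect a secondary safety comparison and the safety reports. The printed definition makes any treated adverse event serious if followed literally, and nothing in the article limits it. The SAE risk ratio may then reflect treated minor events, and not necessarily to the same degree in both arms.

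Size and direction are unknown. The figures above rest on assumed risks, on independence of serious and minor events, and on literal application at every site; narrower application at some sites would shrink the effect. The primary cognitive outcomes and the sample size do not depend on this. The change is worth making because it is cheap and settles what the SAE comparison measures.

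**What to change.** Reword the final criterion to: *or is a medically important event that jeopardises the subject or requires intervention to prevent one of the outcomes listed above*. Carry the same text into the guidance for the case report form, and analyse SAEs by that definition, applied in the same way to all recorded events at all sites and without regard to treatment arm. Leave the hospitalisation criterion as it is, and let reports already filed stand. If the full protocol already holds the limiting words, the sponsor need only confirm this and correct the published definition.

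The cost is one clause, a note to sites, and a uniform classification for the analysis. The downside is that fewer events take the expedited SAE route to ethics committees, which deserves a thought in a paediatric trial without a monitoring board. All of them remain recorded as adverse events and stay in the overall adverse event comparison.

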## Methods

### Study setting

Study preparations have been initiated in 22 centres with expertise in the treatment of rare paediatric epilepsy syndromes across 12 European countries. Details of the participating centres can be found under the “Trial status” section at the end of this manuscript.

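### The protocol names SUSARs as suspected reactions but defines them as probable ones, so a serious, unexpected event that is only suspected triggers no competent-authority, 7-day or EudraVigilance report

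*Protocol article*

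**What the plan says.** All the relevant text is in the Safety and tolerability section of the protocol article.

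- **The name.** Both study drugs are described as long used and well characterised, and on that ground "the occurrence of suspected unexpected serious adverse reactions (SUSARs) is unlikely". The category is spelled out as one of *suspected* reactions.
- **The definition.** "SUSARs are SAEs that probably relate to the investigational drug and that are unexpected with regard to the drug used".
- **Uncertain causality.** "If there is any uncertainty regarding relation between the study medication and a severe adverse event, this will be discussed within the steering committee". The sentence gives no default classification and no time limit. It speaks of a *severe* event, whereas the term defined just before it is *serious* adverse event.
- **Route for every SAE.** "SAEs will be reported to the ethics committee that approved the study within 15 days". No causality condition is attached.
- **Routes for SUSARs.** "SUSARs will be reported to the ethics committee and competent authority of the country where the SUSAR occurred within 15 days"; "for fatal or life-threatening cases, a preliminary report will be sent within 7 days"; and "The SUSAR will be reported to the EMA EudraVigilance database".
- **Periodic route.** A safety update report (DSUR) goes each year to the ethics committees and competent authorities.

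The Monitoring section adds that the trial has no data safety and monitoring board, because it was classed as low risk.

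**The concern.** *Suspected* and *probably* are different causality thresholds. An assessor can suspect that a drug contributed to an event without thinking it more likely than not. Such an event fits the category as named and fails the category as defined. Since the fastest reports hang on SUSAR status, the choice of word decides whether a competent authority hears of the event in days or only in a periodic summary.

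The setting makes this more than a point of style. The participants are children aged 2 to 12 with an epileptic encephalopathy, in whom seizures and continuing regression can belong to the disease itself. Separating a drug effect from the disease will often be uncertain, so intermediate causality judgements are to be expected. There is no independent safety board. The one interim analysis waits until the primary outcome is available in half of the required patients, and the Discussion reports slower recruitment than expected. Expedited single-case reports are therefore an important early signal to regulators, though not the only safeguard.

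**Working it through.** No arithmetic enters beyond the reporting intervals. The check is to follow one type of event through the stated rules and see which of them apply.

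**The event.** It is serious by the protocol's definition and unexpected for the drug. A relation to the drug is suspected but not judged probable.

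**Step 1: is it a SUSAR?** By the expanded name, yes. By the working definition, no, because that definition needs a probable relation. The working definition is the one a site or monitor would apply.

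**Step 2: which reports does the text then require?**

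| Report | If judged probable | If suspected, not probable |
|---|---|---|
| Approving ethics committee, 15 days | Yes | Yes, through the SAE rule |
| Competent authority, 15 days | Yes | Not required |
| Preliminary report, 7 days, if fatal or life-threatening | Yes | Not required |
| EudraVigilance | Yes | Not required |
| Annual DSUR to ethics committees and authorities | Yes | Yes, if the event is listed there; the only stated route to the authority |

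Three rows change with the threshold. The ethics committee's 15-day report and the annual report do not.

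**Step 3: what is the delay to the authority?** A probable case reaches the authority within 15 days, with a preliminary report within 7 days if it is fatal or life-threatening. For a case that is only suspected, the stated route is a yearly report. An event just after one report would wait for the next, so the upper end is about 12 months. This assumes that the annual report lists the event (its contents are not described) and that nobody reports beyond what the text requires.

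**Step 4: does the sentence on uncertain cases close the gap?** It sends such cases to the steering committee for discussion. It does not say how they are classified in the meantime, or by when. It therefore neither excludes them from SUSAR status nor secures their reporting on time. Its trigger is also unclear, because *severe* is not a defined category in this section and *serious* is.

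**The case against.** The case on the other side has real content.

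- **The event is not hidden.** A reader might infer that events which are only suspected miss the 15-day reports altogether. The text does not support that: every SAE goes to the approving ethics committee within 15 days, whatever its causality. This objection stands, and it limits the point to the other three routes.
- **Steering committee discussion is not exclusion.** One might also infer that uncertain cases are downgraded or that the clock stops. Nothing says so, and the discussion could equally end in SUSAR classification. What remains is only that no interim handling is stated. Detailed committee timelines may well sit in the full protocol, and their absence from an article would not be a finding by itself. The article does, however, print the definition, and its threshold disagrees with the name it has just given.
- **Other safeguards exist.** Reporting is to follow GCP. The investigator must inform participants and ethics committees if risks may outweigh benefits. Monitors check all SAEs and SUSARs. These matter, but a general reference to GCP does not override a specific definition in the same paragraph, and a monitor who applies that definition would pass a suspected case that was not expedited.
- **SUSARs are expected to be unlikely.** That probably keeps the number affected small. It also keeps the correction cheap, and it does not justify the wrong threshold for the few that occur.
- **Reporting across countries.** Because the direct report goes only to the country of occurrence, and the setting is "22 centres with expertise in the treatment of rare paediatric epilepsy syndromes across 12 European countries", a reader might infer that other countries are left uninformed. The document does not support this. EudraVigilance entry and the annual report reach further, and a duty to notify every country directly would rest on rules outside the document.

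**Conclusion.** The point holds in a limited form. The protocol states two different causality thresholds for the same category, and the operative one is the stricter. Under it, a serious, unexpected event that is suspected but not judged probable triggers none of three reports: the competent-authority report within 15 days, the 7-day preliminary report if fatal or life-threatening, and EudraVigilance entry. The ethics committee's 15-day report is unaffected.

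The size is three of the five stated routes for each such event, and a delay to the authority of up to about 12 months instead of 7 or 15 days. The document gives no causality scale and no expected event counts, so the share of events affected cannot be estimated. The conclusion rests on reading the definition literally. It does not bear on the efficacy analysis or the sample size.

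**What to change.** 1. Reconcile the name and the definition: a SUSAR is an SAE that is unexpected and for which a relation to the study drug is suspected, not only probable.
2. State that events of uncertain causality are handled as suspected, with the 7- and 15-day deadlines running, while the steering committee discusses them.
3. In that same sentence, replace *severe* by *serious*, so that the trigger matches the defined term.

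The change is confined to wording in the safety section and leaves design, sample size and treatment as they are. The downside is a few more expedited reports, some of which will later be judged unrelated. The protocol's own expectation that SUSARs are unlikely suggests that this burden is small.

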### Sample size calculation

A formal sample size calculation is hampered by the fact that no previous trials with these interventions have been performed. Our recently performed meta-analysis of published cases with epileptic encephalopathy with ESES provides the basis for estimating the difference in proportions of successfully treated patients that might be expected between corticosteroids and benzodiazepines. In our meta-analysis, treatment success was defined as improvement in EEG (at least 25% decrease in SWI) or cognition (10 IQ points or improvement defined by author). Differences in proportions were 25–30% between the two treatment groups in favour of corticosteroids. However, these results are of limited value because of the small sample size in the included studies and their mostly retrospective design.

In the RESCUE ESES study, we aim to include a total of 130 children, of whom 65 will be randomised to treatment with corticosteroids and 65 to clobazam. This sample size permits to detect a difference of 25% in the proportion of successfully treated patients between the two treatment arms (for example 50% vs 25%). In fact, 116 patients are needed to identify this difference with a power of 80% and a two-sided alpha of 5%, and we additionally account for a possible dropout rate of 10%.

As mentioned above, success is defined as improvement of 0.75 of the standard deviation of either IQ or the cognitive sum score. Differences of this magnitude have been reported in earlier observational (non-randomised) studies in this area [28]. Displaying the primary outcome as a dichotomous value (instead of a continuous value) will lead to a conservative estimation of the difference in effect. Therefore, our sample size calculation is likely to be an overestimation of the required number of patients for the continuous outcomes.

For continuous outcomes, we can detect standardised mean differences or Cohen’s *d* of around 0.5 (power = 80%, two-sided alpha of 5%). For Cohen’s *d*, an effect size of 0.2 to 0.3 is considered a “small” effect, around 0.5 a “medium” effect, and above 0.8 a “large” effect [29]. This means that “medium” effects on secondary outcomes can be detected by our trial including 130 children. Furthermore, as the primary outcome can also be displayed as a continuous variable (IQ or cognitive sum score), this also applies to analysis of the primary outcome as a continuous variable.

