### Monitoring

Because both treatments in this trial are also given as part of standard patient care, the study was classified as a (pragmatic) low-risk trial. A data safety and monitoring board (DSMB) was therefore not required. At the coordinating centre, UMC Utrecht, monitoring is performed by the hospital’s dedicated team of study monitors (not directly related to the study team). In the participating centres, monitoring is performed by clinical trial units affiliated with the European Clinical Research Infrastructure Network (ECRIN). An initiation visit, annual monitoring visits, and a close-out visit are performed in all centres in accordance with GCP guidelines. Monitoring procedures include a general control of the conduct and progress of the trial, study files, as well as a 100% check of the presence and correctness of informed consent forms, SAEs, and SUSARs as well as source data verification for 10% of collected data. A written monitor report will be provided by the monitor after each monitoring visit and includes a list of proposed measures and recommendations to ensure compliance with the study protocol.

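### A half-way comparison of effectiveness decides whether the trial continues, on a verbal criterion only, with no named reviewers of the unblinded result and a sample size built for a single look

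*Protocol article*

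**What the plan says.** In the protocol article, Methods, Safety and tolerability, an interim analysis takes place when the primary outcome is available for half the required patients. Its purpose is "to evaluate whether there are unexpectedly large differences in effectiveness and unexpected side effects in both treatment groups". Its consequence is stated directly: "This analysis will form the basis to determine whether continuation of the trial is ethically justified". No p-value, boundary or effect size accompanies the criterion.

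Sample size calculation states that "116 patients are needed to identify this difference with a power of 80% and a two-sided alpha of 5"%, and aims for 130 children, 65 per arm. It mentions no interim look. Statistical analysis compares categorical outcomes by Fisher's exact test and continuous outcomes by t test or Mann-Whitney U test, and states no adjusted level.

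Monitoring classifies the trial as low risk because both treatments are standard care, and concludes: "A data safety and monitoring board (DSMB) was therefore not required". The monitors described there check trial conduct, consent forms, serious adverse events and source data. No section says who runs or sees the interim comparison. Under Treatment, patients and treating physicians are unblinded, while neuropsychological and EEG assessors are blinded.

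**The concern.** A comparative look at effectiveness that can end the trial is a chance to declare a difference early. Without a bound set beforehand, the people deciding judge what counts as unexpectedly large after seeing the data. Two things are then at stake.

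- **The result itself.** Repeated looks can raise the false-positive rate, and a trial stopped on a striking half-sample difference will tend to overstate the effect.
- **The conduct of the rest of the trial.** The Treatment section allows switching arms after 3 months on the impression of parents or physician, and switchers stay in the intention-to-treat analysis (Recruitment and promotion of participant retention). The Discussion reports that some families declined because they strongly preferred one arm. If an interim trend became known, it could affect both switching and enrolment.

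The reason given for having no DSMB, that both drugs are in ordinary use, concerns safety. It does not address who may see an unblinded efficacy comparison half-way through.

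**Working it through.** **Inputs from the protocol.** Response rates "for example 50% vs 25"%, two-sided alpha 5%, power 80%, dropout 10%, 130 randomised 1:1 (all Sample size calculation); interim at about half the primary-outcome data (Safety and tolerability); Fisher's exact test for categorical and t test for continuous outcomes (Statistical analysis).

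**1. The plan's own figure.** Two proportions, pooled variance under the null, mean rate 0.375, no continuity correction:

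n per arm = [1.960·√(2·0.375·0.625) + 0.842·√(0.5·0.5 + 0.25·0.75)]² / 0.25² = [1.342 + 0.557]² / 0.0625 = 57.7, so 58 per arm and 116 in total.

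116 / 0.9 = 128.9, so 129; 130 is the next even number. The stated 116 is thus reproduced exactly by a fixed single-look formula at the full 5%. It contains no allowance for an interim look.

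**2. Overall type I error, normal approximation.** With half the information at the look, the interim and final statistics have correlation √0.5 = 0.707. The overall error is P(|Z1|>c1 or |Z2|>c2). If the final test stays at 5%:

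| Rule at the look | Overall two-sided error |
|---|---|
| p<0.05 | 8.3% |
| p<0.02 | 6.1% |
| p<0.01 | 5.5% |
| p<0.005 | 5.2% |
| p<0.001 | 5.02% |

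Pairs of levels (look, then final) that hold 5%: O'Brien-Fleming 0.0052 and 0.0480; Haybittle-Peto 0.001 and 0.0498. These figures suit a t-test comparison.

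**3. Overall type I error, Fisher's exact test.** Exact binomial enumeration of both looks, p≤0.05 at each, common response rates of 25%, 37.5% and 50%:

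| Per arm (look, final) | Both looks | Final test alone |
|---|---|---|
| 29, 58 | 4.7–4.9% | 3.1–3.2% |
| 32, 65 | 5.0–5.5% | 2.9–3.5% |

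The second look adds about 1.6 to 2.4 percentage points, but Fisher's test starts well below 5% and absorbs most of it.

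**4. Overstatement after an early stop.** True rates 50% and 25%, 29 per arm, Fisher p≤0.05 at the look, all outcomes enumerated. The better arm is declared superior about 39% of the time, and the mean observed difference in those cases is about 37 points against a true 25. At p≤0.001 this happens about 5% of the time. A strict bound makes overstated early stops rare; it does not make the few that occur less overstated.

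**5. What the verbal criterion might mean.** With 29 per arm and a mean rate of 37.5%, the standard error of the difference is √(2·0.375·0.625/29) = 0.127. An observed difference of 25 points, the planned one, gives z = 0.25/0.127 = 1.97, about p=0.05. A p<0.001 bound would need about 3.29·0.127 = 0.42, or 42 points. The wording does not say where between or beyond these the threshold lies.

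**The case against.** The strongest reply has four parts.

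- **A condensed article.** Boundaries and access rules often sit in a SAP or the full protocol, neither of which is shown, and either might hold a rule. That is fair, and the absence of a number is not by itself the point. The point rests on what is stated: a continuation decision based on effectiveness, a verbal criterion for it, a single-look sample size, and an explicit decision against a DSMB on grounds that do not cover this look.
- **The planned test.** A reader might infer that the trial's error rate is 8.3%. The documents do not support that. The figure needs a p<0.05 rule at the look, which is nowhere stated, and a t-type test. For the dichotomous outcome on which the sample size rests, Fisher's test keeps two looks at 5% close to nominal. This objection stands.
- **The criterion may be strict.** The expected difference is already 25 points, so an unexpectedly large one should exceed it, and stopping only for harm would not inflate alpha. This stands only in part: at half the sample, just exceeding 25 points is roughly a p=0.05 criterion, and the text names effectiveness beside side effects.
- **Who decides.** A reader might infer that those running the open-label trial make the decision, or that the final test spends the whole 5%. Neither is stated. The reviewers are unnamed, an independent data manager exists (Data collection), and the 5% is given for the sample size only. Blinded outcome assessors also limit bias in the primary outcome. Any effect of leaked results on switching or enrolment is therefore a risk, not something the text shows.

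**Conclusion.** The point holds in this limited form: the stated stopping criterion is fixed badly. Effectiveness at half-way can end the trial on a purely verbal test, the sample size makes no provision for that look, and the reviewers are unnamed while a DSMB is excluded.

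The size of any inflation cannot be fixed from the documents. With the final test left at 5%, it runs from about 5.02% (p<0.001 at the look) to about 8.3% (p<0.05) for a continuous analysis. For the dichotomous outcome under Fisher's test, even p≤0.05 at both looks gives 4.7–5.5%. The overstatement of effect applies to the dichotomous outcome too: about 37 points observed against 25 true, if the rule were p≤0.05 with 29 per arm. These figures assume one endpoint and a look at half the information. How the two co-primary outcomes are handled is a separate issue and is not included.

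**What to change.** Replace the verbal criterion by one of two statements, before the interim data are seen:

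- effectiveness can stop the trial at the look only if a strict pre-set bound is crossed, for example Haybittle-Peto with p<0.001, or an O'Brien-Fleming-type bound, with the matching final level (0.0498 or 0.0480 respectively); or
- the look cannot stop the trial for efficacy.

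Add an access rule. The comparison is run by someone outside the treating team, for example the independent data manager named under Data collection, and investigators are told only that the trial continues unless the bound or a safety concern is met.

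The cost is a few sentences and existing staff. The final level barely moves, so 130 patients need not change. The small downside is that an early stop for efficacy then needs very strong evidence.
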